**Figure 2 F2:**
[figure not shown]
Study design. MACS, Manual Ability Classification System; GMFCS, Gross Motor Function Classification System; PEDI, Pediatric Evaluation of Disability Inventory; VR, virtual reality; n: sample size; tDCS, transcranial direct current stimulation; D0-D11, days of interventions in which D0 is the baseline, D1 to D10 are the days of interventions and the D11 is the day of the final assessments. Participants and sampling.

Thirty-six participants will be recruited through referral by the coordinators of three clinics in Brazil: *Intensiva, Intertherapy*, and *Therapies*, located in São Paulo state. Those interested in participating will undergo a detailed screening using the eligibility criteria for enrolment in the study.

The sample size was calculated using statistical software (GPower 3.1.5) on the main outcome measure (i.e., the motor score). This calculation was based on data from one study with a group of individuals with CP who received tDCS (32). The power was 0.80; the alpha was 0.05; and the effect size was 0.65 (Cohen's d). The sample estimation indicated that 28 participants would be necessary (i.e., 14 per group). With an adjustment to allow for a withdrawal rate (20%), we will recruit 36 participants.

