Study type interventional allocation	Randomised
Masking	Triple-blinded
Assignment	Crossover
Primary purpose	Treatment
Date of first enrolment	March 2019
Target sample size	35
Recruitment status	Recruiting
Primary outcome(s)	Motor skills improvement
Key secondary outcome(s)	HRV improvement

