### Overview of the Study Design

A triple-blinded randomised controlled crossover trial with a 1:1 allocation ratio will be conducted, and all participants will undertake non-immersive VR tasks and active or sham tDCS. Groups A–S will start with 10 daily sessions of tDCS-active combined with VR tasks for 20 min. After a 1 month washout, this group will be reallocated to another 10 daily sessions of 20 min with sham tDCS combined with VR tasks. Meanwhile, groups S–A will carry out the opposite protocol (participants will start an allocated 10 sessions of sham tDCS combined with VR tasks, and after a 1 month washout period will be reallocated to 10 sessions of active tDCS combined with VR tasks). The 1 month washout period has been used and was shown to be sufficient to reset the effects of the first 10 sessions in Biabani et al. (31). Figure 2 summarises the planned experimental design. This research protocol follows the SPIRIT recommendations.

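### The sample size of 28 (14 per group) does not follow from the printed inputs under a standard t-test: two groups of 14 have about 38% power, and for the crossover contrast the stated 80% cannot be verified

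*Protocol article*

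**What the plan says.** The sampling text after the caption of Figure 2 in the protocol article reports a G*Power calculation on a motor score, with an effect size taken from one earlier study of tDCS in cerebral palsy. The inputs are: "The power was 0.80; the alpha was 0.05; and the effect size was 0.65", the last being labelled Cohen's d. The result is: "The sample estimation indicated that 28 participants would be necessary (i.e., 14 per group"). The text continues: "With an adjustment to allow for a withdrawal rate (20%), we will recruit 36 participants". Table 1 gives a different recruitment figure: "Target sample size 35".

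The Overview of the Study Design describes the trial as follows: "A triple-blinded randomised controlled crossover trial with a 1:1 allocation ratio will be conducted". Each participant receives ten active and ten sham sessions, separated by a one-month washout. The Statistical Analysis section plans ANOVA within and between groups, or Friedman and Wilcoxon tests within groups and Kruskal–Wallis and Mann–Whitney tests between groups. It does not name a within-participant active-sham contrast. The sample-size text does not give the test, the sidedness, the scale of d or a within-person correlation.

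**The concern.** The article prints both the inputs and the answer, so a reader should be able to get from one to the other. With a plain t-test that is not possible, either for two groups or for pairs.

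This is the document's only power justification, and the two natural readings err in opposite directions. If the 80% is attached to a comparison of two groups of 14, power is overstated about twofold. If it is attached to the paired contrast with 0.65 as dz, power is understated. The phrase about 14 per group, together with the between-group tests in the Statistical Analysis section, leaves open which comparison the 80% is meant to cover. Whether a null result is informative depends on that.

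**Working it through.** **Inputs.** Power 0.80, alpha 0.05, d = 0.65, evaluable N = 28 (14 per group), 20% withdrawal, 36 to be recruited: sampling text after Figure 2. Target of 35: Table 1. 1:1 two-sequence crossover: Overview of the Study Design. Two-sided testing is my assumption, as sidedness is not stated; one-sided results are given beside it. All t-test power figures use the noncentral t distribution.

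**1. Attempt to reproduce 28 as a two-group comparison.** Noncentrality = d × √(n/2), df = 2n − 2.
- At n = 14 per group: 0.65 × √7 = 1.72, df 26, power 38.1% (one-sided 51.2%).
- At n = 18 per group, that is all 36 with no withdrawals: 0.65 × √9 = 1.95, df 34, power 47.4%.
- Required for 80%: 39 per group, 78 in total (one-sided 30 per group).
- Smallest d with 80% power at 14 v 14: about 1.10.

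This does not give 28.

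**2. Attempt to reproduce 28 as a paired comparison with 0.65 as dz.** Noncentrality = dz × √N, df = N − 1.
- At N = 28: 0.65 × √28 = 3.44, df 27, power 91.2% (one-sided 95.6%).
- Required for 80%: 21 (one-sided 17). A two-sequence crossover t with N − 2 df also needs 21. A Wilcoxon test needs about 22, or about 25 in the worst case.
- Smallest dz with 80% power at N = 28: 0.55.

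This does not give 28 either.

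**3. Paired comparison with 0.65 on the between-person SD.** dz = d / √(2(1 − ρ)), where ρ is the active-sham correlation, which the article does not state.

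| ρ | dz | N for 80% | Power at N = 28 |
|---|---|---|---|
| 0 | 0.460 | 40 | 65% |
| 0.2 | 0.514 | 32 | 75% |
| 0.3 | 0.549 | 28 | 80% |
| 0.4 | 0.593 | 25 | 86% |
| 0.5 | 0.650 | 21 | 91% |
| 0.7 | 0.839 | 14 | 99% |

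At ρ = 0.30, dz = 0.65 / √1.4 = 0.549, and 28 is recovered with power 80.0%. With N − 2 df the match is at ρ = 0.31. At ρ = 0.5, dz equals d, which is why step 2 and that row agree.

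**4. Repeated-measures ANOVA.** Take f = d/2 = 0.325 with two groups and m measurements.
- Within factor or interaction: λ = f²Nm / (1 − ρ). With m = 4, ρ = 0, N = 28: 0.1056 × 112 = 11.8. The required N is 28.
- Between factor: λ = f²Nm / (1 + (m − 1)ρ). With m = 3, ρ = 0, N = 28: 0.1056 × 84 = 8.87. The required N is 28.
- At ρ = 0.3 the same two settings need 20 and 42, so the match depends on zero correlation.

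**5. Withdrawal.** 28 / (1 − 0.20) = 35, the figure in Table 1. The next even number, which 1:1 allocation would favour, is 36.

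**The case against.** A reader might infer that the stated power is wrong whichever way the trial is analysed. The document does not support that. The figure of 21 holds only if 0.65 is dz (or, equivalently, if ρ = 0.5), and the article says neither. On the between-person scale, 28 gives 80% power at a correlation of about 0.30. That is not the only route: the Statistical Analysis section plans ANOVA, and two repeated-measures settings also return 28. Zero correlation between repeated measurements on one child is implausible, and nothing shows that those settings were used, but they rule out any claim that a single assumption explains the number.

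A reader might also take the 14 per group as proof that a parallel two-sample test was intended. It is not: in a 1:1 two-sequence crossover, 28 participants are 14 per sequence, and the phrase can be plain allocation.

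The 38% is conditional too. It applies to an unadjusted comparison of 14 v 14 with d on that outcome's SD. No first-period-only analysis is described, and the Statistical Analysis section does not say whether its groups are sequences or treatment conditions. The primary outcome is change from baseline. If 0.65 is on the raw-score SD and the comparison is baseline-adjusted (effective d = 0.65 / √(1 − r²)), power at 14 per group rises to about 48%, 64% and 79% for baseline correlations r of 0.5, 0.7 and 0.8.

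Finally, a condensed article may leave the test and the correlation to a fuller document. That is fair, and their absence alone is not the point.

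What remains is that the printed answer does not follow from the printed inputs under either standard t-test, and every rescue needs an input that is not printed. The between-group tests are in the document, and the 80% cannot be carried over to an unadjusted version of them.

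**Conclusion.** The point holds in this form. Under a standard two-sided t-test, d = 0.65, 80% power and alpha 0.05 lead to 39 per group or to 21 pairs, not to 28; one-sided testing gives 30 per group or 17 pairs.

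For the within-participant active-sham contrast, 28 evaluable participants have about 91% power if 0.65 is dz, and 65% to 99% for correlations of 0 to 0.7 if it is a between-person d. The stated 80% lies inside that range, so it is unverifiable but not shown to be false. On that reading there is a shortfall only if the correlation is below about 0.30.

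For an unadjusted comparison of two groups of 14, power is about 38% (47% at 18 per group), and the 80% claim does not apply. The correlations are assumptions shown as a range; the article gives none.

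The difference between 35 and 36 is minor. It is consistent with rounding up to an even number and has no bearing on the main point.

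**What to change.** In the sample-size paragraph:

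1. Restate the calculation for the within-participant active-sham contrast. Name the test and its sidedness, say whether 0.65 is a within-person (dz) or between-person d, and give the assumed correlation with its basis in the cited study.
2. Report the power of 28 evaluable participants on that basis: about 91% if 0.65 is dz, or the value for the assumed correlation, with the 65% to 99% range, if it is a between-person d.
3. Say that the 14 are participants per sequence.
4. Add that an unadjusted between-group comparison of 14 v 14, as the between-group tests in the Statistical Analysis section may be, has about 38% power at d = 0.65 and is not covered by the 80% claim.
5. Use one recruitment target, 35 or 36, in the abstract, the sampling text and Table 1.

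The cost is wording only. No extra participants are needed.

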### Inclusion Criteria

Participants will be included if they have: the agreement to participate in the research from themselves [by signing assent form (33)] and their legal guardians (by signing a consent form); a clinical diagnosis of CP will be carried out by a neuropaediatric clinician; with GMFCS levels I to IV and MACS I to IV; age ranging from 4 to 14 years.

### Exclusion Criteria

Participants will be excluded if they (1) do not understand the tasks—the understanding of the task will be evaluated through five attempts at each task in VR, because even with a low intelligence quotient (IQ) a large number of the children and adolescents can understand virtual tasks and interact with improved performance; (2) motor difficulties that impede the completing of the virtual tasks; (3) cardiac diseases that impede the assessment of HRV; (4) surgery or use of an upper limb spasticity inhibitor during the last 6 months; and (5) a metal prosthesis in the head.

### Withdrawal Criteria

Participants will be withdrawn from the study if they are not willing to continue, cannot be present on the day of the experiment, or miss two treatment sessions out of 10 (four in total).

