**Figure 1 F1:**
[figure not shown]
SPIRIT: Description of the study protocol, schedule of enrolment, interventions, and assessments. ^*^List of specific timepoints in this row.

**Table 1 T1:** Trial characteristics based on WHO Trial Registration Data Set.

**Data category**	**Trial information**
Primary registry and trial identifying number	ClinicalTrials.gov, ID: NCT04044677
Date of registration in primary registry	05 August 2019
Secondary identifying numbers	Ethical Committee of the University of São Paulo, under the number CAAE: 99577318.0.0000.5390
Source(s) of monetary or material support	Coordenação de Aperfeiçoamento de Pessoal de Nível Superior–Brasil (CAPES)
Primary sponsor	University of São Paulo–USP
Secondary sponsor(s)	NA
Contact for public queries	[name], [name]
Contact for scientific queries	[name], [name]
Public title	Virtual reality therapy and transcranial direct current stimulation in cerebral palsy
Scientific title	Effect of combined virtual reality therapy and transcranial direct current stimulation on children and adolescents with cerebral palsy
Country of recruitment	Brazil
Health condition(s) or problem(s) studied	Cerebral palsy
Interventions	Group 1 will start with 10 sessions of active tDSC combined with VR tasks. After a 1 month washout, this group will be reallocated to another 10 sessions with sham tDCS combined with VR tasks. Meanwhile, group 2 will carry out the opposite protocol (i.e., participants will start an allocated 10 sessions of sham TDCS combined with VR tasks, and after a 1 month washout period will be reallocated to 10 sessions of active tDCS combined with VR tasks).
Key inclusion and exclusion criteria	Inclusion criteria: the agreement to participate in the research from themselves and their legal guardians; a clinical diagnosis of CP will be performed by a neuropaediatric clinician; with Gross Motor Function Classification System (GMFCS) levels I to IV; and Manual Ability Classification System (MACS) I to IV; age range 4–14 years. Exclusion criteria: do not understand the tasks; motor difficulties that impede the completing of the virtual tasks; cardiac diseases that impede the assessment of heart rate variability (HRV) and surgery; use of an upper limb spasticity inhibitor during the previous 6 months; metal prosthesis on the head. Withdrawal criteria: participants will be withdrawn from the study if they are not willing to continue cannot be present on the day of the experiment, or miss two treatment sessions.

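### Missed sessions remove randomised children from the study, so later outcomes are lost according to attendance, and the two statements of the rule disagree

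*Protocol article*

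**What the plan says.** The Withdrawal Criteria section opens: "Participants will be withdrawn from the study if they are not willing to continue". It then adds those who "cannot be present on the day of the experiment, or miss two treatment sessions out of 10 (four in total". The row on key inclusion and exclusion criteria in Table 1 gives the same list but ends at "cannot be present on the day of the experiment, or miss two treatment sessions", with neither a denominator nor a total.

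The Overview of the Study Design sets a 1:1 randomised crossover with 10 sessions per period. Sessions start after allocation, so the missed-session rule can act only after randomisation. Assessments are placed at D0, D5 and D11. No section says that a withdrawn child will still be assessed, or that data already collected will be dropped.

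The sample size paragraph (after Figure 2) says "The sample estimation indicated that 28 participants would be necessary (i.e., 14 per group", and then "With an adjustment to allow for a withdrawal rate (20%), we will recruit 36 participants". It does not tie the 20% to an expected rate of missed sessions.

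**The concern.** A child who reaches the attendance limit leaves the study, not just the stimulation programme. The remaining assessments in that period are then not made, and after a withdrawal in period 1 the whole second period is missing. That child gives no within-child active-sham contrast, which is the comparison a crossover exists to provide.

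The loss is decided by behaviour after randomisation. Attendance over two blocks of consecutive weekday sessions may depend on how well the child tolerates stimulation or on whether the family sees a benefit, and both could differ between active and sham. No analysis plan can recover outcomes that were never measured.

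The rule also cannot be applied uniformly, because its two statements lead to different decisions for the same child.

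**Working it through.** **The two statements side by side**

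- A child misses one session in block 1 and one in block 2. Table 1, read over all sessions, withdraws the child. The Methods text, read per block of 10, keeps the child.
- Within the Methods text, if two misses in a block trigger withdrawal, a child enters block 2 with at most one miss and leaves at the second miss there. The total never exceeds 1 + 2 = 3, so a limit of four could not operate as a separate trigger.
- Absence on the day of the experiment is a further ground. It is not stated whether this means an assessment day or any session day.

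**The plan's own figure**

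14 / (1 − 0.20) = 17.5, rounded up to 18 per group, gives 36. This reproduces. From 36, up to 36 − 28 = 8 children (8/36 = 22.2%) can be lost and still leave 28.

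**Withdrawal from missed sessions alone**

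The absence rate p per session is an assumption, since the documents give none. Absences are first taken as independent.

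- Two in either block of 10: q = 1 − (1−p)^10 − 10p(1−p)^9, and over two blocks 1 − (1−q)². At p = 5%, q = 1 − 0.5987 − 0.3151 = 0.086, giving 0.165. At p = 10%, q = 1 − 0.3487 − 0.3874 = 0.264, giving 0.458.
- Two of 20: 1 − (1−p)^20 − 20p(1−p)^19. At 5% this is 1 − 0.3585 − 0.3774 = 0.264; at 10% it is 0.608.
- Four of 20: P(X ≥ 4) with X binomial(20, p). This is 0.016 at 5% and 0.133 at 10%.

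| Reading | p = 3% | 5% | 8% | 10% | p that uses up 20% | Expected left of 36 at 5% / 10% |
|---|---|---|---|---|---|---|
| Two in either block of 10 | 6.8% | 16.5% | 34.0% | 45.8% | 5.6% | 30.1 / 19.5 |
| Two of 20 | 12.0% | 26.4% | 48.3% | 60.8% | 4.1% | 26.5 / 14.1 |
| Four of 20 | 0.3% | 1.6% | 7.1% | 13.3% | 11.7% | 35.4 / 31.2 |

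The last column is 36 × (1 − withdrawal). The chance of losing more than 8 of 36 under the per-block reading is 13% at p = 5%, 40% at 6% and 91% at 8%.

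These figures leave out unwillingness and missed assessment days. If absence from any of four D0/D11 visits also counts, the per-block reading reaches 20% at p = 3.4%. If the day of the experiment means any of the 20 session days, 1 − (1−p)^20 = 0.20 at p = 1.1%.

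**Clustered absences**

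Let each child's absence rate follow a beta distribution with mean p and intraclass correlation r, so that a = p(1/r − 1) and b = (1−p)(1/r − 1), with r assumed between 0.05 and 0.2.

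- At p = 10%, the per-block figure falls from 46% to 33–41% and two of 20 falls from 61% to 38–52%. Four of 20 rises from 13% to 19–21%.
- At p = 5%, the three figures are 17–19%, 20–26% and 6–10%.

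**The case against.** The strongest reply has four parts.

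**Nothing says data are deleted.** A reader might infer that outcomes already collected are thrown away, or that the analysis is restricted to adherent children. The text supports neither. It ends participation, names no analysis set, and leaves the handling of withdrawals to documents not shown. This part stands. What remains is that outcomes due after withdrawal are not collected.

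**The size rests on an assumption.** A reader might also infer that the 20% allowance will be exceeded. At 5% absence the Methods rule read per block gives 16.5%, inside the allowance. The four-of-20 reading stays inside even at 10% if absences are independent. Table 1 states no denominator and describes blocks of 10 elsewhere, so two of 20 is only a literal reading. All this stands: exceeding 20% is possible, not predicted.

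**Falling below 28 need not cost power.** The stated inputs are "The power was 0.80; the alpha was 0.05; and the effect size was 0.65" (Cohen's d). If that is a paired standardised difference, a two-sided paired t-test needs 21 children for 80% power. Even at 40% loss, 36 × 0.6 = 21.6 leaves 21 whole children and 80.9% power. This stands on that reading of d, so loss of power is not the main charge.

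**Bias is not demonstrated.** The rule is the same in both sequences and the trial is blinded. Severity is essentially fixed within a child, so losing severe cases mainly affects generalisability. This stands in part. Tolerance and perceived benefit can still differ between active and sham, but the direction and size are unknown.

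The words about four in total may also be shorthand for two per block over two blocks. One clarifying sentence would settle that, but it would not reconcile the text with Table 1.

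**Conclusion.** The point holds in this form. The protocol withdraws randomised children from the study for missed sessions or absence and provides no further assessment. Later D11 and second-period outcomes are thus lost on a basis set after randomisation. This is a risk of bias in the active-sham contrast, not a demonstrated bias. The Methods text and Table 1 disagree, and the Methods text is unclear within itself.

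On size, with independent absence of 5% to 10% per session, the three readings give withdrawal from 1.6% to 60.8% against an allowance of 20%. The reading and the unknown absence rate together decide whether 36 recruits leave 28. Clustering lowers the two larger 10% figures and raises the smallest, so it narrows the spread without removing it. The main harms are outcomes missing according to attendance and a rule that cannot be applied consistently.

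**What to change.** 1. Reconcile the Withdrawal Criteria section with Table 1 so that one rule is stated, with its denominator, and say what the day of the experiment means. Which limit is appropriate is for the investigators and is not proposed here.
2. Separate stopping sessions from leaving the study. A child who reaches the limit is still invited to the remaining scheduled assessments unless consent or assent is withdrawn.
3. State whether such a child may still enter period 2. Assessments without period-2 sessions do not restore the within-child contrast.
4. Analyse all randomised children as randomised, with all available data. The repeated-measures ANOVA/MANOVA and Friedman/Wilcoxon tests in the Statistical Analysis section need complete sets in their usual form. A method that accepts incomplete periods is therefore needed, for example a mixed model with sequence, period and treatment. This would be a change to that section. Define an attendance-based set and use it as a sensitivity analysis.

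The cost is revised wording, a few visits already in the schedule and a little more analysis work. The estimated effect may be slightly diluted by children with incomplete attendance.

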### Randomisation

Participants will be randomly allocated to either group A-S (active tDCS and VR tasks) or group S-A (sham tDCS and VR tasks) with a 1:1 allocation defined by a website (randomization.com). As we will have the participant's characteristics, immediately after the randomisation the age and motor function (GMFCS/MACS) will be compared between groups; if the groups are not homogeneous, a new randomisation will be carried out. This protocol will be repeated until there is no difference between age and GMFCS amongst groups (in a maximum of first three attempts at randomisation, we always have homogeneous groups). Randomisation will be under the control of a blinded investigator who will be the only person allowed to manage the electronic security file of the randomisation to locate the individuals. (More details about this can be found in the section that follows). The investigator will be blind to the group to which the participant is allocated.

